### Outcome assessment

Outcomes will be assessed at baseline and 1, 3 and 6 months later. Outcome data will be obtained from all randomised participants, in so far as this is possible, regardless of compliance with the trial protocol. Outcome measurements will be made by an assessor blinded to allocation. The participants, as well as physiotherapists and investigators involved in the trial, will be asked to avoid giving information that could reveal participant's allocation to the blinded assessor. After each assessment the assessor will be asked if he or she was blinded to allocation and will be asked to guess which group the participant was allocated to.

At the baseline assessment, demographic and injury details will be recorded. Classification of fracture severity (severe or not severe) will be based on the number of malleoli fractured [20] and the presence of dislocation: bi- or tri-malleolar fractures and any fractures with dislocation will be classified as severe. The assessor will classify fracture severity by examining the radiology entries in the hospital records or, if these are not available, by examining plain radiographs taken before and after the fracture reduction. Two psychological scales will also be used: depression, anxiety and stress will be measured using the Depression, Anxiety, Stress Scales 21-item [24], and pain catastrophising will be assessed using the Pain Catastrophising Scale [25].

The primary outcomes will be activity limitation and quality-adjusted life years. Activity limitation will be measured with the Lower Extremity Functional Scale [26] which involves the participant rating the degree of difficulty in performing 20 functional activities on a 5-point scale ranging from 0 ('extreme difficulty or unable to perform activity') to 4 ('no difficulty'). The scale has excellent test-retest reliability (intraclass correlation coefficient (ICC) 0.94), is sensitive to change and has high internal consistency and construct and concurrent validity for people with ankle fracture [27]. Quality-adjusted life years will be measured by the Assessment of Quality of Life instrument, which is designed to measure health-related quality of life and to be the descriptive system for a multi-attribute utility instrument. The Assessment of Quality of Life measures five dimensions: illness, independent living, social relationships, physical senses and psychological well-being, all of which have been shown to be orthogonal and unidimensional [28]. The Assessment of Quality of Life has been shown to be internally consistent (alpha = 0.81) and has a comparative fit index of 0.90 [28], and is reliable and more sensitive to health status than other multi-attribute utility instruments [29].

Secondary outcomes will be the number of days to pain-free walking, the number of days to return to full pre-fracture work, return to pre-fracture work and leisure activities, ankle dorsiflexion range of motion, pain, walking speed, physical activity, and global perceived effect of treatment (Table 1).

**Table 1 T1:** Secondary outcome measures assessed at baseline, 1, 3 and 6 months, unless otherwise stated.

Outcome	Description of assessment
Number of days to pain-free walking	Participants will be given a calendar to mark the first day they can walk pain-free for 10 meters to calculate the number of days elapsed from the day of randomisation to pain-free walking [5].
Number of days to return to full pre- fracture work	Participants who worked prior to fracture will be given a calendar to mark the first day they return to their pre-fracture work to calculate the number of days elapsed from the day of randomisation to return to full pre-fracture work.
Return to pre-fracture work and leisure	Self-reported percentage return to full pre-fracture work and leisure, where 0% is 'not participating at all' and 100% is 'returned to full level'.
Ankle dorsiflexion range of motion	Measured using the weight-bearing lunge method [23] at baseline and 1-month.
Pain	Pain on equal weight-bearing and on stair descent measured using a numerical rating scale (0 to 10), where 0 is 'no pain' and 10 is 'worst pain you ever had', at baseline and 1-month.
Walking speed	Unaided walking speed over a 10 m distance using a stop watch at baseline and 1-month.
Physical activity	Physical activity will be measured using the International Physical Activity Questionnaire-Short Form [39]. This questionnaire will be used to classify participants into one of the three activity levels (low, moderate or high) and calculate the metabolic equivalent (MET) minutes per week.
Global perceived	Perceived effect of treatment will be measured on an 11-point scale from -5,
effect of treatment	'vastly worse', to +5, 'completely recovered' at 1, 3 and 6 months.

Participants in the *Rehabilitation *and *Advice *groups will complete exercise diaries. Physiotherapists treating participants in the *Rehabilitation *group will complete treatment logs. Participants in the *Advice *group will be asked at each assessment if they sought rehabilitation or physiotherapy services. Participants' perceptions of the credibility of the interventions will be determined by questions administered to all participants at the 6-month follow-up. At the 6-month assessment, participants will also be asked open-ended questions about adverse events.

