The Cochrane review identified only two randomised controlled trials which investigated effects of rehabilitation after the immobilisation period [6,15]. Two other trials have been recently completed [5,16]. These trials concluded that adding passive stretch or manual therapy to an exercise program does not improve clinical or economic outcomes compared to exercise alone [5,6,15], and found no overall benefit of participating in an exercise program [16]. However, in the trial that compared an exercise program to usual care, benefits of the exercise program could have been underestimated as there was a high uptake of physiotherapy (a mean of 7 physiotherapy appointments) by participants from the usual care group [16]. In addition, the trial only included people whose ankle had been treated surgically [16].

It is still unclear if some sub-groups could benefit more from rehabilitation than others. Nilsson et al [16] compared the effects of rehabilitation on Olerud-Molander Ankle Score (range 0 to 100) in those aged < 40 years and those ≥ 40. There was no difference in effects of rehabilitation at 6 months. However the effect of rehabilitation at 12 months was greater in people aged < 40 than in those aged ≥ 40 (mean difference in effect 16.9 points, 95% CI 5.6 to 28.2). This finding should be considered provisional until it is replicated in other studies. We postulate that participation in a rehabilitation program may particularly benefit older women (aged over 50 years) as they are more likely to suffer from osteoporosis [17], and physical performance [18] and physical activity [19] also decline with age. The severity of fracture has also been found to influence outcome in ankle fracture [20], which raises the idea that rehabilitation should be offered selectively. In this case, it could be argued that people with more severe fracture would have worse outcomes and, consequently, would benefit more from a rehabilitation program.

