## Methods/Design

The trial will be an assessor-blinded pragmatic randomised controlled trial. Three hundred and forty two participants will be randomly allocated to one of two groups: an *Advice *group and a *Rehabilitation *group (~171 in each group). Outcomes will be assessed at baseline, 1, 3 and 6 months by a blinded assessor (Figure 1).

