## Discussion

The EXACT trial will provide evidence on the effectiveness of rehabilitation after ankle fracture. Participants receiving the *Rehabilitation *intervention will receive an individually tailored and exercise-based physiotherapy program and participants receiving the *Advice *intervention will not, because the intent is to compare the effects of these two alternatives when they are administered as usually applied in the clinic. We will not match the number of treatment sessions for the *Advice *group because, given the pragmatic orientation of the trial, it is more important to replicate current clinical practice. A pragmatic trial design [33,34] was chosen to enable easy translation of the research findings into clinical practice.

Our trial incorporates features that minimise bias, including concealed random allocation and blinded data analysis [35]. Blinding of outcome assessment may be particularly important in exercise trials such as ours, where the blinding of participants and therapists is not possible [36]. The primary outcomes (activity limitation, quality-adjusted life years etc) will be self-reported by participants who are not blinded. However the assessors who elicit primary outcome data, and who collect secondary outcome data such as ankle dorsiflexion range of motion and walking speed, will be unaware of group allocation. Consequently the assessment of outcome is partially blinded. Procedures recently suggested to achieve blinding in pragmatic physiotherapy trials will be used in our trial, including asking participants not to reveal their group allocation to assessors when booking follow-up appointments and at the start of each assessment, and restricting assessor access to trial data which indicates group allocation (computer files will be password protected and paperwork will be in a separate locked filing cabinet) [37]. We will also confirm the success of assessor blinding by asking the assessor if he or she was blinded to allocation and to guess which group the participant was allocated to after each assessment.

The sample size will be large enough to provide precise estimates of treatment effects. Importantly, the trial is adequately powered to investigate whether the effects of rehabilitation differ across sub-groups of participants [38]. In our trial we will determine if treatment effects are influenced by fracture severity and by the age and gender of participants.

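### The direct question about seeking physiotherapy goes to the Advice arm only, at visits made by a blinded assessor: a possible cue to allocation and an uneven record of co-intervention

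*Protocol article*

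**What the plan says.** The text after Table 1 in the protocol article (Outcome assessment) sets out how treatment received is tracked. Both arms keep exercise diaries, and physiotherapists treating Rehabilitation participants keep treatment logs. The Advice "group will be asked at each assessment if they sought rehabilitation or physiotherapy services". No equivalent question is set for Rehabilitation participants. The article does not say who asks it, on which form, or at what point in the visit.

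Methods/Design describes those visits: "Outcomes will be assessed at baseline, 1, 3 and 6 months by a blinded assessor". Outcome assessment repeats it: "Outcome measurements will be made by an assessor blinded to allocation". Participants, treating physiotherapists and investigators "will be asked to avoid giving information that could reveal participant's allocation to the blinded assessor". The Discussion adds further measures, among them "restricting assessor access to trial data which indicates group allocation", by means of password-protected files and separately locked paperwork. There is also a check: "After each assessment the assessor will be asked if he or she was blinded to allocation", and the assessor then guesses the group.

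Separately, the Economic evaluation section has a resource-use questionnaire at 1, 3 and 6 months, with no limit by arm. Table 2 shows that it covers visits to general practitioners, other health professionals, community services and complementary practitioners. The Statistical analysis section compares utilisation between the arms.

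**The concern.** A question put to one arm only cannot be asked by someone who does not know the arm. Asking it marks an Advice participant; leaving it out marks a Rehabilitation participant. The answer may also disclose treatment received, which participants have been asked not to reveal to the assessor.

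The assessor matters here because participants are not blinded. The Discussion relies on "the assessors who elicit primary outcome data, and who collect secondary outcome data such as ankle dorsiflexion range of motion and walking speed" being unaware of allocation, and accepts that blinding is only partial. The primary conclusions rest on activity limitation and quality of life at 3 months. A cue given at the 1-month visit would come before those data are elicited.

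A second, lesser matter is co-intervention. The Background section explains that an earlier trial may have underestimated benefit because its usual-care group had "a mean of 7 physiotherapy appointments". A reader of this trial will therefore want to know how much physiotherapy each arm actually had. That comparison is cleaner if both arms are prompted in the same way.

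**Working it through.** The document gives no figure for this point, so the check is to set its statements side by side and then bound the exposure.

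**1. Does the rule work against the blinding?**
- The direct question goes to one arm, at every assessment.
- The assessments are made by a blinded assessor.
- No other person is named to ask it, and no separate form or position after the outcome measurements is given.
- The listed safeguards are requests to participants and staff not to reveal allocation, and restricted access to files and paperwork. None expressly covers an arm-specific item inside the visit.
- The after-visit check can detect lost blinding but does not prevent it.

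So if the assessor asks the question or sees the form, allocation is disclosed. If someone else handles it out of the assessor's sight, it is not. The article settles neither.

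**2. Which outcomes could be touched?**
- Table 1 measures dorsiflexion, pain and walking speed at baseline and 1 month only. These are exposed only if the item comes before them at the 1-month visit.
- The 3-month primary outcomes are exposed if the item comes before them at that visit, or if the assessor from month 1 returns at month 3. The article does not say whether the same assessor returns.

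**3. Exposure.** Inputs: 342 participants, about 171 per arm (Methods/Design), and three follow-up visits. I take each assessment to mean each follow-up, since a baseline question would make little sense.
- Visits where the item is present (Advice): 171 × 3 = 513.
- Visits where its absence is informative (Rehabilitation): 171 × 3 = 513.
- Total: 513 + 513 = 1,026 = 342 × 3, before losses.
- Visits at the primary time point: 342 before losses.

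These are ceilings on the number of visits with a possible cue. They are not a count of unblinded assessments, and they cannot be turned into a bias in outcome points.

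**4. Is outside treatment recorded equally?**
- Advice arm: the direct question at each assessment, plus the resource-use questionnaire.
- Rehabilitation arm: the resource-use questionnaire, plus logs from the physiotherapists treating them. Table 2 takes physiotherapists' time from those physiotherapists' own report. Nothing says that the logs or reports cover outside providers.

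For physiotherapy outside the trial, that is two prompts in one arm, one of them specific, against a single general prompt in the other. If the general prompt misses some visits, outside physiotherapy would be under-recorded more in the Rehabilitation arm. The documents do not show by how much.

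**The case against.** The strongest reply is that the article never says the blinded assessor asks the question. The sentence is passive, the assessor's stated task is outcome measurement, and this item is not listed as an outcome. The Discussion restricts the assessor's access to allocation-revealing data, which is compatible with the item being handled elsewhere. Who administers which form is detail that an article commonly leaves to the full protocol.

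Much of this stands. A reader might infer that the assessor is certainly unblinded from month 1; the document does not support that. What remains is that the article does fix one thing itself: the question is for one arm only, at the blinded assessor's visits. In the same paragraph it directs the credibility questions to everyone. The point therefore rests on a stated rule and not only on missing detail.

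A reader might also infer that outside treatment in the Rehabilitation arm goes unasked. It does not: the resource-use questionnaire covers both arms, and utilisation is compared between them. Nor does the asymmetry rule out a fair treatment comparison. The primary analysis is by intention to treat and is not described as using this item. The Background section's worry about physiotherapy in a usual-care group is a good reason to ask the Advice arm; it does not show that asking is a mistake.

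Finally, much of what remains at 3 and 6 months is self-report by unblinded participants, so the assessor's influence may be small. That is fair, and it limits the severity.

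**Conclusion.** The concern holds in a limited form. An arm-specific question is placed at blinded visits without an express safeguard, and co-intervention is prompted unevenly, though it is not left unrecorded. The blinding part depends on the assessor asking the item or seeing the form. For the 3-month primary outcomes it depends also on the order within that visit or on the same assessor returning. The ascertainment part is secondary and depends on the general category missing visits that a direct question would catch.

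The possible exposure is at most 1,026 visits before losses. The size of any bias cannot be computed from the document. Severity is moderate to minor: worth changing because the change is cheap, but not a flaw that undermines the trial.

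**What to change.** Replace the Advice-only question with one identical item for both arms at 1, 3 and 6 months, asking about physiotherapy or rehabilitation received outside the trial program. Put it on the existing resource-use questionnaire, self-completed and returned so that the blinded assessor neither asks nor sees it, for example sealed or collected by unblinded staff. State this handling in the Outcome assessment section.

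This removes the cue to allocation and makes the record of co-intervention symmetric. It changes neither the design, the sample size nor the analysis. The cost is one item moved to an existing form, about a minute more per Rehabilitation participant, and care in wording so that Rehabilitation participants do not count their trial sessions.

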### Economic evaluation

The economic evaluation will consist of cost-effectiveness and cost-utility analyses. Costs will be measured in terms of direct costs to the health system and out-of-pocket costs to the participants over a 6-month period, and collected in a questionnaire at the 1, 3 and 6 month follow-up period. From an economic perspective, costs are measured by resource use. This allows the identification of the opportunity cost of resources used, that is, what could have been achieved had those resources been allocated to the best alternative use. In this trial the costs of the interventions and any out-of-pocket costs incurred by participants will be identified, measured and valued. Table 2 indicates the type of resources which will be captured, the sources of data, and proposed methods of valuation.

**Table 2 T2:** Assessment of resource use.

Type of resource	Method of assessment	Method of valuation
Physiotherapists' time	Physiotherapists' report	Salary rates plus on-costs for physiotherapists using published prices
Equipment	Questionnaires at 1, 3, 6 months	Manufacturer's price (depreciated over 3 years)
Medication, visits to general practitioners and other health professionals, hospitalisation, visits to emergency department	Questionnaires at 1, 3, 6 months	Published prices (e.g. Pharmaceutical Benefits Scheme and Medicare Benefits Schedule reimbursement) and/or actual costs to participants
Visits to community services or alternative or complementary health practitioners	Questionnaires at 1, 3, 6 months	Actual costs to participants

The cost-effectiveness analysis will use the Lower Extremity Functional Scale [26] as a measure of effectiveness. The cost-utility analysis will use the Assessment of Quality of Life instrument as a measure of utility.

### Statistical analysis

Analyses will be conducted by 'intention-to-treat' (i.e. all available data from all randomised participants will be analysed in the group to which the participant was allocated). Multiple imputation will be used for missing data. To test the effects of intervention on continuous outcomes (activity limitation, quality of life, return to pre-fracture work and leisure, physical activity (metabolic equivalent minutes per week), ankle range of motion, pain, walking speed, and global perceived effect of treatment), between-group comparisons will be conducted using longitudinal mixed models [30,31]. The independent variables will be a dummy-coded variable indicating group membership, the time at which the measurement was taken (four times, dummy-coded as three variables, with the baseline time as the referent category), and the three time-by-group interactions. The effect of rehabilitation at each of the three follow-up time points is estimated with the relevant interaction term. The model will incorporate random intercepts to account for the dependence of repeated measures. Survival analysis will be used to estimate between-group differences in days to pain-free walking and days to return to full pre-fracture work. Odds ratios will be calculated for physical activity (level), satisfaction with trial treatment, and adverse events.

In a second analysis, designed to test the influence of fracture severity on treatment response, additional terms (fracture severity and the interactions of fracture severity with the group and time variables) will be entered into the model. The effect of fracture severity on treatment response will be determined by examining the interactions between group membership, fracture severity and the time variables. A similar analysis will test the influence of participant age and gender on treatment response. Participants will be divided into women aged over 50 and others. Again, additional terms (age/gender and the interactions of age/gender with the group and time variables) will be entered into the model. The effect of age/gender on treatment response will be determined by examining the interactions between group membership, age/gender and the time variables.

The primary conclusions about effectiveness of rehabilitation will be based on between-group comparisons of activity limitation and quality of life at 3 months. The primary conclusions about whether fracture severity and age and gender influence the effectiveness of intervention will be based on the interactions between these factors and effects of rehabilitation for activity limitation and quality of life at 3 months.

The economic evaluation will examine differences between participants in the *Rehabilitation *and *Advice *groups in terms of costs incurred and changes in perceived activity limitation (cost-effectiveness analysis) or utility gained (cost-utility analysis). The incremental cost-effectiveness (utility) ratio (ICER) will be calculated as: ICER = (*C_R _*- *C_A_*)/(*U_R _*- *U_A_*), where C is average cost, U is the average effectiveness or utility score, and subscripts R and A denote the *Rehabilitation *and *Advice *arms. The *Rehabilitation *program can be said to be cost-effective relative to *Advice *about exercise if it (a) produces less activity limitation or greater utility at a lower cost or (b) the cost per activity limitation avoided or per quality-adjusted life years gained (i.e. the incremental cost-effectiveness (utility) ratio) is less than some threshold value (e.g. $50,000). Bias-corrected bootstrapped estimates (1,000 replications) will be used to test for the difference in mean costs and to obtain 95% confidence intervals for between-group differences in mean costs. Between-group differences in utilisation will be tested using Fisher's exact test. Sensitivity analyses will be undertaken to explore the robustness and validity of the results. Both costs and outcomes will be varied in line with results from similar studies reported in the literature and the upper and lower limits of estimates from this trial.

To establish the predictors of outcome after ankle fracture, univariate linear regression will be used to examine the relationship between seven baseline variables (fracture severity, pain, ankle range of motion, mobility, depression, anxiety and stress, and pain catastrophising) and activity limitation at 1-month and 6 months after removal of immobilisation. A multivariate linear prediction model will be developed using methods described by Harrell [32].

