## Background

Ankle fracture, fracture of the distal tibia and/or fibula, is the second most common ankle injury after ankle sprain [1]. The incidence of ankle fracture is at least 5 per 10,000 person-years across all ages [2,3], but is higher in young men (13 to 28 per 10,000 person-years) and older women (16 to 20 per 10,000 person-years). The orthopaedic management depends on the severity of the fracture, but generally involves immobilisation of the ankle in a cast or a brace for about 6 weeks [4]. Surgical fixation is required in about 50% of cases [5,6].

The disabling sequelae of ankle fracture and the subsequent immobilisation frequently affect people's ability to return to work and sport. Our recent study showed that people with ankle fracture had significant activity limitation after the period of immobilisation (mean Lower Extremity Functional Scale score of 33.6, where no activity limitation receives a score of 80) and one-third were unable to walk without crutches [5]. Impairments include pain [5,6], stiffness [7,8], weakness [9-11] and swelling [12,13]. Rehabilitation programs are often provided to address these sequelae and can commence as soon as the fracture has been stabilised (i.e. during the period of immobilisation) or, more often, after the period of immobilisation (i.e. when bone union has occurred). Typically a post-immobilisation program consists of stretch, manual therapy, exercise, gait training and advice [5,6].

There is limited evidence on the effects of rehabilitation interventions for ankle fracture. A Cochrane systematic review has evaluated the effects of rehabilitation interventions applied during or after the period of immobilisation. It concluded that commencing weight bearing during the immobilisation period and wearing a brace that can be removed to allow gentle ankle exercise may improve outcome after ankle fracture [14].

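### Global perceived effect has no baseline measurement, so the baseline-referent interaction model assigned to it does not identify its treatment effect; three other secondary outcomes have only two of the model's four visits

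*Protocol article*

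**What the plan says.** The Statistical analysis section sets out one model for a named list of continuous outcomes. The list ends "ankle range of motion, pain, walking speed, and global perceived effect of treatment), between-group comparisons will be conducted using longitudinal mixed models". Time is entered as "four times, dummy-coded as three variables, with the baseline time as the referent category", together with a group indicator and three time-by-group products. The estimand is then fixed: "The effect of rehabilitation at each of the three follow-up time points is estimated with the relevant interaction term". Dependence within a participant is handled as follows: "The model will incorporate random intercepts to account for the dependence of repeated measures". No different model is given for any continuous outcome.

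Table 1, in the Outcome assessment section, takes four visits as the default and lists exceptions. Global perceived effect is scored on an 11-point scale running from "vastly worse', to +5, 'completely recovered' at 1, 3 and 6 months", with no baseline score. Walking speed is "Unaided walking speed over a 10 m distance using a stop watch at baseline and 1-month". Ankle dorsiflexion range and pain follow the same two-visit schedule.

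**The concern.** The model needs a baseline observation in each group, because each interaction is a group difference at follow-up minus the group difference at baseline. Global perceived effect has no baseline, and could not have one, since nobody can rate the effect of a treatment not yet given. The rule for reading its effect therefore points at a quantity that the data cannot supply.

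This is not detail left to a later document. The article names the outcome, the coding and the term to be read, and the three do not fit together. The analyst will have to improvise, and the result reported would depend on how the software or the analyst resolves the redundancy. One plausible resolution would hide a sustained benefit.

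The mismatch for range of motion, pain and walking speed is of the same kind but milder: the text promises effects at three follow-ups, and these outcomes have one.

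**Working it through.** The plan gives no figure to reproduce here. The check is whether the stated fixed effects can be estimated from the visits that each outcome has.

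**Inputs.** Model terms come from the Statistical analysis section; visits come from Table 1. The columns are the intercept, group *g*, time dummies *t1*, *t3*, *t6*, and products *g·t1*, *g·t3*, *g·t6*: 1 + 1 + 3 + 3 = 8.

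**Rank by visit schedule** (two groups, so the number of cell means is 2 × the number of visits):

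| Outcome | Visits | Cell means | Rank of 8 columns | Interactions identified |
|---|---|---|---|---|
| Outcomes with all four visits | 0, 1, 3, 6 months | 8 | 8 | all three |
| Global perceived effect | 1, 3, 6 months | 6 | 6 | none |
| Range of motion, pain, walking speed | 0, 1 month | 4 | 4 | 1 month only |

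**Why global perceived effect loses two ranks.** With no baseline rows, every row has exactly one time dummy equal to 1. So *t1 + t3 + t6* equals the intercept, and *g·t1 + g·t3 + g·t6* equals *g*. These are two exact dependencies: 8 − 2 = 6. What remains identified is the sum of the group coefficient and the interaction at each visit, which is the plain group difference there.

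**What an analyst might then report.** Take a constant benefit of 1 point at 1, 3 and 6 months (an illustrative value).

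- If 1 month becomes the referent, the interaction at 3 months is 1 − 1 = 0 and at 6 months 1 − 1 = 0. The group main effect is 1, and the plan does not read it.
- If the intercept and group columns are dropped instead, the three interactions are 1, 1 and 1, which is correct.
- If a minimum-norm (generalised inverse) solution is taken, the group coefficient is 0.75 and each interaction 0.25. Only their sum, 1, has meaning.

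The same data and the same stated model thus give interaction readings of 0, 1 or 0.25.

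**Two-visit outcomes.** Dropping the empty 3- and 6-month terms leaves four columns and four cell means, which is full rank. The 1-month interaction is the difference between groups in mean change from baseline, and it is unbiased under randomisation.

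Its precision can be compared with a baseline-adjusted comparison. Assume a common standard deviation σ at both visits and correlation ρ between them. Per participant, the change score has variance 2σ²(1 − ρ), and the baseline-adjusted residual has variance σ²(1 − ρ²). The ratio is (1 − ρ²) / [2(1 − ρ)] = (1 + ρ)/2, which never exceeds 1. At an assumed ρ of 0.5 it is 0.75. The documents give no value of ρ.

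**The case against.** The strongest reply is that a competent analyst would see that there is no baseline and report the difference at each follow-up. The plan does ask for an effect at each of three time points, and with 1 month as referent only two interactions exist, so re-referencing would itself depart from the text. As shown above, one way of removing the redundancy returns the right answer. This stands in part: a null result is one possible outcome, not the expected one. It does not rescue the stated rule, which identifies nothing without a choice the plan has not made. Random intercepts do not help, because the fault lies in the fixed effects. The general statement "Multiple imputation will be used for missing data" does not help either, because a perceived effect before treatment is not a missing value.

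For the two-visit outcomes, it is fair to say that omitting empty terms is routine and leaves the 1-month estimate valid. That stands in full.

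A reader might go further on walking speed. The Background reports from an earlier study that "one-third were unable to walk without crutches" after immobilisation. With 342 participants, 342/3 = 114, so one might infer that about 114 baseline speeds would be imputed and the effect biased upward. The documents do not support this, for three reasons.

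- They do not say that inability to walk unaided is recorded as missing, and such scoring is detail that an article may leave out.
- Baseline ability precedes randomisation and is balanced in expectation.
- Simulation does not show upward bias as a rule. It used 342 participants, a correlation of 0.5, the slowest third missing at baseline and a true average effect of 0.50 SD. With a homogeneous effect, a random-intercept fit averaged 0.51 and multiple imputation 0.50. With effects of 0.80 in the missing third and 0.35 in the rest, they averaged 0.45 and 0.46. With effects of 0.20 and 0.65, multiple imputation averaged 0.54. The shift is modest, and its direction depends on heterogeneity that nobody knows.

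**Conclusion.** The point holds for global perceived effect. The stated design has rank 6 of 8 and none of the three interactions the plan would read is identified. This follows from the coding and Table 1 alone and rests on no numerical assumption. The missed constant benefit is conditional on 1 month being made the referent.

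For range of motion, pain and walking speed, the finding is a mismatch of specification. The 3- and 6-month effects do not exist, the 1-month effect is sound, and what a different analysis offers is precision only.

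All four outcomes are secondary. The primary conclusions rest on activity limitation and quality of life at 3 months, to which Table 1's visit exceptions do not apply, so they are untouched.

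**What to change.** State the model by the visits each outcome has.

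- **Global perceived effect:** fit group-by-time means at 1, 3 and 6 months (six fixed-effect parameters, full rank), keep the random intercept, and report the between-group difference at each visit.
- **Range of motion, pain and walking speed:** compare groups at 1 month with adjustment for the baseline value. Under the assumptions above, this is at least as precise as the change-from-baseline interaction.
- **Outcomes with all four visits:** this point requires no change.

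The cost is two or three sentences. No extra data, visits or participants are needed.
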